## Dissemination Policy

Study results will be published in a medical journal accessible to the medical community and the public. However, individual participant data will not be made available even after the trial results are published. Researchers who provide a methodologically sound proposal approved by an independent review committee can direct their requests to the principal investigator.

This trial protocol is drafted per the SPIRIT 2013 checklist.

## Appendix

**Figure 1.** Nine-item Shared Decision Making Questionnaire (SDM-Q-9).

**[Example]** Please indicate which health complaint/problem/illness the consultation was about:

**[Example]** Please indicate which decision was made:

Nine statements related to the decision-making in your consultation are listed below. For each statement please indicate how much you agree or disagree.

|                                                                                                    |                                                 |                                               |                                               |                                            |                                            |                                              |
|----------------------------------------------------------------------------------------------------|-------------------------------------------------|-----------------------------------------------|-----------------------------------------------|--------------------------------------------|--------------------------------------------|----------------------------------------------|
| 1. My doctor made clear that a decision needs to be made.                                   | completely disagree
 | strongly disagree
 | somewhat disagree
 | somewhat agree
 | strongly agree
 | completely agree
 |
| 2. My doctor wanted to know exactly how I want to be involved in making the decision.       | completely disagree
 | strongly disagree
 | somewhat disagree
 | somewhat agree
 | strongly agree
 | completely agree
 |
| 3. My doctor told me that there are different options for treating my medical condition.    | completely disagree
 | strongly disagree
 | somewhat disagree
 | somewhat agree
 | strongly agree
 | completely agree
 |
| 4. My doctor precisely explained the advantages and disadvantages of the treatment options. | completely disagree
 | strongly disagree
 | somewhat disagree
 | somewhat agree
 | strongly agree
 | completely agree
 |
| 5. My doctor helped me understand all the information.                                      | completely disagree
 | strongly disagree
 | somewhat disagree
 | somewhat agree
 | strongly agree
 | completely agree
 |
| 6. My doctor asked me which treatment option I prefer.                                      | completely disagree
 | strongly disagree
 | somewhat disagree
 | somewhat agree
 | strongly agree
 | completely agree
 |
| 7. My doctor and I thoroughly weighed the different treatment options.                      | completely disagree
 | strongly disagree
 | somewhat disagree
 | somewhat agree
 | strongly agree
 | completely agree
 |
| 8. My doctor and I selected a treatment option together.                                    | completely disagree
 | strongly disagree
 | somewhat disagree
 | somewhat agree
 | strongly agree
 | completely agree
 |
| 9. My doctor and I reached an agreement on how to proceed.                                  | completely disagree
 | strongly disagree
 | somewhat disagree
 | somewhat agree
 | strongly agree
 | completely agree
 |

Martin Härter & Isabelle Scholl, University Medical Center Hamburg-Eppendorf, Germany

[figure not shown]

This work is licensed under the Creative Commons Attribution-NonCommercial-NoDerivatives 4.0 International License. To view a copy of the license, visit <http://creativecommons.org/licenses/by-nc-nd/4.0/legalcode>

**Figure 2.** Six-item State-Trait Anxiety Inventory Questionnaire (STAI-6).

|                         | None | Somewhat | Moderately | Very Much |
|-------------------------|-------------|-----------------|-------------------|------------------|
| 1 I feel calm    | 1           | 2               | 3                 | 4                |
| 2 I am tense     | 1           | 2               | 3                 | 4                |
| 3 I feel upset   | 1           | 2               | 3                 | 4                |
| 4 I am relaxed   | 1           | 2               | 3                 | 4                |
| 5 I feel content | 1           | 2               | 3                 | 4                |
| 6 I am worried   | 1           | 2               | 3                 | 4                |

**Figure 3. Patient Education Assessment.**

**Patient Education Assessment**

**Mark the correct answer (all questions are underlined):**

1. Is the colon a hollow organ: **True** or **False**
2. Which part of your colon contains the disease?  
Right (ascending) colon  
Transverse colon  
Left (descending) colon  
Sigmoid colon  
Rectum
3. Which part of your colon will the surgeon remove?  
Right (ascending) colon  
Transverse colon  
Left (descending) colon  
Sigmoid colon  
Rectum
4. This surgery will be done via: **One large incision** or **Multiple small incisions**
5. Will you have an ostomy bag after surgery? **True** or **False**
6. What is an anastomotic leak?  
  
Leakage of stool content from the part of the colon that was joined back together  
Leakage of urine from my bladder  
Leakage of stool from the colon that was not operated on
7. Which of the following is a potential complication of your surgery?  
Difficulty walking  
Internal bleeding  
Cough  
Pinched nerve
8. Which of the following can be damaged during this type of surgery?  
Ureter  
Liver  
Spine

**Figure 4.** BRIEF: Health Literacy Screening Tool.

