## Inclusion/Exclusion Criteria

Patients will be recruited from the colorectal surgery clinics of Vanderbilt University Medical Center, a tertiary care hospital in Nashville, TN, USA. Our inclusion and exclusion criteria are as follows:

| INCLUSION                                                              | EXCLUSION                       |
|------------------------------------------------------------------------|---------------------------------|
| Age over 18 years                                                      | Non-English speaker             |
| Scheduled for partial or complete resection of the colon and/or rectum | Unable to give informed consent |

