## Outcome Measurements

**Primary Outcome Measures:** The difference in the levels of shared decision-making using the validated SDM-Q-9 questionnaire (Figure 1) and the differential change in anxiety levels post-intervention using the validated STAI-6 questionnaire (Figure 2).

**Secondary Outcome Measures:** A differential change in the patient knowledge level captured by our 13-question Patient Education Assessment survey (Figure 3) and evaluating if the change is consistent when categorized by health literacy scores based on the BRIEF: Health Literacy Screening Tool (Figure 4).

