## Statistical Considerations

Sample size: Since we do not have prior data in this patient cohort to appropriately power or simulate our analysis, we used the mean and standard deviation of SDM-Q-9 in the literature [86.7 ( $\pm 11.6$ )]. To ensure that this study has adequate power to detect a clinically meaningful effect size and provide data for future studies, we assume a 5% risk of type I error and a 20% risk of type II error, a 1:1 enrollment ratio, and a targeted increase of 3 times the minimal clinically important difference ( $4^{17}$ ). This means that 20 patients needed to be allocated to each arm. Since this intervention has not been utilized in colorectal patients before, we target an expected rejection rate of 50%, meaning 80 patients should be approached (40 in each arm).

Data analysis plan: Patient characteristics will be compared between the 3D-printed model and standard care arms with the chi-squared test for categorical variables and the Student's t-test for comparisons between continuous variables. The postintervention SDM-Q-9, the preintervention and postintervention STAI-6, and the Patient Education Assessment Questionnaire scores will be compared between the study arms using the restricted maximum-likelihood estimation to account for the intraclass differences. The postintervention score will be treated as a dependent variable, while the preintervention score will be treated as a covariate. A similar subgroup analysis will be conducted after dichotomizing health literacy into adequate (17-20) and inadequate or marginal ( $<17$ ) groups. The level of significance will be at  $\alpha = 0.05$  throughout the manuscript. Statistical analyses will be performed using Stata (version 17, StataCorp LLC, College Station, TX). We do not plan on conducting any interim analysis.

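### Items 2 and 3 of the knowledge form ask for one bowel segment, but patients having multi-segment resections are eligible and cannot answer completely

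*Protocol*

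**What the plan says.** **The form (Protocol, Appendix, Figure 3).** The heading instruction is "Mark the correct answer (all questions are underlined". Item 2 asks "Which part of your colon contains the disease" and item 3 asks "Which part of your colon will the surgeon remove". Both offer the same five choices: right, transverse, left, sigmoid and rectum. Neither has a choice for the whole colon, for colon and rectum together, or for more than one segment, and neither invites several marks.

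**Who can enrol (Protocol, Inclusion/Exclusion Criteria).** Eligible patients are those "Scheduled for partial or complete resection of the colon and/or rectum".

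**What the form is for.** Under Outcome Measurements the secondary outcome begins "A differential change in the patient knowledge level captured by our 13-question Patient Education Assessment survey". Better understanding of the procedure is also part of the primary hypothesis and of Aim 2 (Specific Aims). The form is given before and after the consultation. The data analysis plan under Statistical Considerations says "The postintervention score will be treated as a dependent variable, while the preintervention score will be treated as a covariate".

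**What is not stated.** The protocol gives no answer key for the form. It does not say whether the electronic version accepts several marks, or how several marks would count.

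**The concern.** The instruction and both item stems are in the singular, while the eligibility criterion expressly admits operations with a plural answer. A patient about to lose the whole colon who understands this perfectly has no listed option that says so.

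Items 2 and 3 are the questions on where the disease is and what will be removed, which a physical model of the colon could plausibly clarify. If they cannot record a gain in some patients, the knowledge comparison loses sensitivity where an effect might be expected. If some patients tick one box and others tick several, part of the score reflects how the instruction was read rather than what the patient knows.

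With six surgeons as the randomised units, and no balancing by operation type described, the share of multi-segment operations could also differ between arms by chance.

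**Working it through.** The plan gives no figure on this point, so there is nothing of its own to reproduce. The check compares the form with the eligibility criterion and asks what a single mark can record.

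**Inputs.** Five answer options in each of items 2 and 3 (Figure 3). Complete resection, and resection of colon and rectum, are eligible (Inclusion/Exclusion Criteria). There are 13 questions by the protocol's count (Outcome Measurements), of which 8 are visible in the copy reviewed. The target is 20 patients per arm (Statistical Considerations).

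**Step 1: what the form can express.** Five segments allow 2^5 − 1 = 31 non-empty sets. One mark can express 5 of them. Not all 31 are realistic operations, but the eligible complete resections are among the 26 that one mark cannot express.

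**Step 2: item 3 answered with one mark.** A strict key requires every removed segment to be marked. A lenient key accepts any removed segment. For an uninformed patient choosing one of the five boxes at random:

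| Planned resection | Strict key: best possible result | Lenient key: chance of a correct guess | Lenient key: room to improve |
|---|---|---|---|
| One segment | correct | 1/5 = 20% | 80% |
| Two segments | wrong | 2/5 = 40% | 60% |
| Whole colon, rectum kept | wrong | 4/5 = 80% | 20% |
| Colon and rectum | wrong | 5/5 = 100% | 0% |

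Under the strict key a single mark records no learning in any multi-segment patient. Under the lenient key the item records little or nothing for complete resections. For two segments it keeps some room, but it cannot separate a patient who knows one of the segments from a patient who knows both. The same reasoning applies to item 2 when disease spans segments.

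**Step 3: largest effect on one patient's score.** Under a strict key with one mark, losing item 3 caps the score at 7/8 = 87.5% of the visible items, or 12/13 = 92.3% of the stated 13. Losing items 2 and 3 caps it at 6/8 = 75%, or 11/13 = 84.6%. So the affected share is at most 2/8 = 25% or 2/13 = 15.4% of items.

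**Step 4: how many patients.** The documents do not give the share of multi-segment operations. Assuming 10% to 30%, the number is 0.10 × 20 = 2 to 0.30 × 20 = 6 per arm.

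**The case against.** The strongest reply is that the protocol states no scoring rule. Nothing bars several marks, and a patient-specific key accepting every applicable segment could score them. Such a key may sit in a statistical analysis plan that is not shown. The risk section describes a computer-based assessment, so the response format depends on an electronic form that is not reproduced. The figure may also be incomplete in the copy reviewed.

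Much of this stands. A reader might infer that multi-segment answers are unscorable or will be marked wrong. The documents do not support that, because it presumes a scoring rule they do not contain. What does not stand is the idea that a key alone settles the matter: it cannot recover information that the form did not ask the patient to give.

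Two other stronger readings are tempting.

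- **A definite shift between arms.** This would require multi-segment patients to be concentrated in one arm, both items to be lost for each of them, and adjustment for the baseline score to remove nothing. The documents show none of these. A multi-segment operation can be done for single-segment disease, leaving item 2 intact. The same form is used at both times with the earlier score as covariate, so part of any difference would be absorbed.
- **No operative plan to score against.** The protocol says that clinical information is collected in REDCap and allows study data to be transferred into it from an institutional data source. Eligible patients already have surgery scheduled. That the variables are not itemised does not show that disease site and planned resection go unrecorded.

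**Conclusion.** The point holds as a defect in the printed instrument. The singular wording and option list of items 2 and 3 do not fit the eligible operations, so a multi-segment patient who follows the instruction cannot answer item 3 completely, nor item 2 when disease spans segments.

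The consequence is limited: at most two items of a secondary outcome in a pilot trial, with neither primary outcome (SDM-Q-9, STAI-6) touched. The expected effect is reduced sensitivity and added noise in the knowledge comparison. Bias would arise only if operation types differed between arms. Six surgeons as clusters make that possible, but nothing in the protocol shows it, and the baseline covariate would absorb part of it.

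The conclusion assumes that patients take the instruction at its word and mark one box, and that the electronic form follows the printed one. The 2 to 6 patients per arm rest on an assumed share of 10% to 30%. The conclusion does not depend on whether the form has 8 or 13 items.

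**What to change.** - Reword items 2 and 3 so that the patient marks every segment that applies, or add options for the whole colon and for colon and rectum.
- Set the electronic form to accept several marks on these two items.
- State the scoring rule: each item is correct only when the marked segments match the disease site (item 2) or the planned resection (item 3) in the clinical record.

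The cost is a small edit before first use and a slightly more detailed scoring key. It needs no extra patients or visits. The edit should precede the first patient, because a later change would mix two versions of the form within one outcome.

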### ***Questions***

**Please circle the answer that best represents your response.**

**1. How often do you have someone help you read hospital materials?**

- a. Always
- b. Often
- c. Sometimes
- d. Occasionally
- e. Never

**2. How often do you have problems learning about your medical condition because of difficulty understanding written information?**

- a. Always
- b. Often
- c. Sometimes
- d. Occasionally
- e. Never

**3. How often do you have a problem understanding what is told to you about your medical condition?**

- a. Always
- b. Often
- c. Sometimes
- d. Occasionally
- e. Never

**4. How confident are you filling out medical forms by yourself?**

- a. Not at all
- b. A little bit
- c. Somewhat
- d. Quite a bit
- e. Extremely

### ***Scoring***

Each item is worth 1 to 5 points depending on their response (as seen in numbers to the left of the answer options). Add the values for the four responses to get a total score, which can range from a minimum of 4 to a maximum of 20. To interpret scores refer to the following:

### ***Interpretation***

**Limited (4-12):** Not able to read most low-literacy health materials; will need repeated oral instructions; materials should be composed of illustrations or videos. Will need low-literacy materials; may not be able to read a prescription label.

**Marginal (13-16):** May need assistance; may struggle with patient education materials.

**Adequate (17-20):** Will be able to read and comprehend most patient education materials.

**Figure 5.** Study schema

[figure not shown]

**Figure 6.** Prototype (the final model will be modular and on a larger scale).

[figure not shown]

Supplement: Supplement 1. — Trial Protocol [file jamanetwopen-e2513187-s001.pdf]
